#### Blinding Method

This is a single-blind study, and patients with diabetes are unaware of their group assignment.

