**Results:**

This study was funded in August 2021 and has received approval from the Ethics Committee of Guang’anmen Hospital, China Academy of Chinese Medical Sciences (2022-022-KY-01). The trial is ongoing, with the first patient enrolled in September 2022. The study is expected to conclude in April 2025. To date, 380 patients have been recruited, with 202 randomized into the study, though no statistical analysis of the data has yet been conducted. A single-blind method is used; nurses are aware of group assignments and intervention plans, while patients remain blinded. Final results are planned for release in the first quarter of 2025.

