**Inclusion criteria**
The primary diagnosis must align with *International Classification of Diseases, Tenth Revision* codes for type 2 diabetes mellitus, specifically in the range of E11.2 to E11.9.Admission criteria must be met for inpatient treatment, as determined by the clinical physician.In cases where patients have concurrent diagnoses of other diseases, if these conditions do not require special treatment during the hospital stay and do not hinder the implementation of the clinical nursing pathway for the primary diagnosis, the patient can be included in that nursing pathway.Informed consent must be obtained from the patient and documented, indicating their understanding and agreement with the proposed care plan.

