#### Implementation of the TCM Nursing Pathway for T2DM

Upon admission, nurses provide admission education and assess the patient’s condition using an evaluation form for the TCM nursing pathway for T2DM. This assessment determines whether the patient qualifies for inclusion in the study. Eligible patients receive the TCM nursing pathway for T2DM. For patients included in the study, nurses ensure that physicians perform a thorough examination upon admission. The TCM nursing pathway form for T2DM is distributed, and patients are informed about their treatment and the nursing plan during hospitalization. This ensures patients understand the medical and nursing measures to be implemented.

During hospitalization, the responsible nurse uses the evaluation form of the TCM nursing pathway for T2DM to develop an appropriate care plan. This plan may include TCM techniques, syndrome differentiation–based dietary therapy, exercise and health practices, herbal prescriptions, and emotional regulation. The study group strictly adheres to the schedule outlined in the TCM nursing pathway for T2DM. Nurses coordinate with relevant departments promptly to complete necessary examinations. The control group receives routine care.

If there are any changes in the patient’s condition, the responsible nurse promptly analyzes and addresses the changes, adjusting the sequence of items in the TCM nursing pathway as necessary. The head nurse checks the implementation of the TCM nursing pathway for T2DM and the routine care plan daily. The head nurse ensures compliance with the nursing pathway protocol and evaluates the quality of care promptly. Relevant data are collected and evaluated at the time of the patient’s discharge.

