## Results

This trial received funding in August 2021 and is currently ongoing. The first patient was enrolled in September 2022, and the study is expected to conclude in December 2024. The trial uses a single-blind design where nurses are aware of group assignments and intervention details, but the patients remain blinded. Final results are planned for publication in the first quarter of 2025.

To date, 380 patients have been recruited, with 172 excluded, resulting in 202 randomized participants (101 in the study group and 101 in the control group). Details on the screening process are provided as a Consolidated Standards of Reporting Trials (CONSORT) flowchart in Multimedia Appendix 2.

This study primarily aims to compare health knowledge, comprehension, and scores between the 2 groups, with the goal of optimizing an innovative model for the TCM nursing pathway for T2DM. The findings are expected to enhance the standardization and precision of clinical nursing practices. The pathway will be validated clinically, combining theory with practice through prospective research to provide high-level clinical evidence. This will contribute to the development of a high-quality TCM nursing pathway, expand the global influence of TCM, and support national economic growth and public health.

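### The described procedures do not support relying on the patient blind, and the control arm, called routine care, appears to be discretionary pathway nursing

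*Protocol article*

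**What the plan says.** **Blinding.** The Protocol article claims a patient blind in three places. Blinding Method says "This is a single-blind study, and patients with diabetes are unaware of their group assignment". The Results paragraph of the Abstract says "A single-blind method is used; nurses are aware of group assignments and intervention plans, while patients remain blinded". The Results section repeats it: "The trial uses a single-blind design where nurses are aware of group assignments and intervention details, but the patients remain blinded".

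**What patients are told.** Under Inclusion criteria, "Informed consent must be obtained from the patient and documented, indicating their understanding and agreement with the proposed care plan". Under Implementation of the TCM Nursing Pathway for T2DM, "The TCM nursing pathway form for T2DM is distributed, and patients are informed about their treatment and the nursing plan during hospitalization", followed by "This ensures patients understand the medical and nursing measures to be implemented". That section lists what the care plan may contain: TCM techniques, diet therapy, exercise, herbal prescriptions and emotional regulation. Study Design says the research team is made up of nurses from the endocrinology department.

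**Control arm.** The Abstract and the Implementation section call it routine care: "The control group receives routine care". The Intervention Plan section instead says that both groups' plans are set out in a pathway form, together with TCM-specific treatments. There, control nurses apply the plan subjectively according to that form, while the study group is held strictly to the TCM pathway.

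**Outcomes.** The primary outcome is a diabetes-specific quality-of-life scale. Patient satisfaction is a secondary outcome, and a satisfaction rate is the basis of the sample size.

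**The concern.** Quality of life and satisfaction rest on the patient's own judgement. Someone who knows that they are receiving the new programme may answer more favourably whether or not it works. A single-blind label tells readers that this route to a positive result is closed. If the procedures do not close it, readers will give both outcomes more credit than the design earns.

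The control arm raises a different question. Pathway versus routine care would test the TCM pathway as a programme. Strict versus discretionary use of a form would test how closely the nurse keeps to it. A positive result means something different in each case, and the article plans to promote the pathway to other hospitals on the strength of the result.

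**Working it through.** The point is textual, and the plan states no figure for it to reproduce. The check sets the relevant statements side by side.

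**Step 1: is there a mechanism behind the patient blind?**

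| Needed for a credible patient blind | What the article describes |
|---|---|
| Care that looks alike in both arms, or a sham | Openly delivered TCM care in the study arm; no sham described |
| Neutral or matched paperwork | A form carrying the name of the experimental pathway |
| Arm-identifying information withheld | Treatment and plan explained so that patients understand them; nothing named as withheld |
| Contact with staff who do not know the arm | Nurses know the assignment, and the research team consists of nurses |

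The blind is asserted three times, and no step is described that would produce it.

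**Step 2: who receives the form?** The Implementation section does not say whether controls are also given it.

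- If only the study arm receives it, holding a form with the intervention's name on it is a cue to assignment.
- If both arms receive a similar form, the form itself is not a cue. The control is then pathway nursing at the nurse's discretion, and the contrast is narrower than the term routine care suggests.

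So the reading that best protects the blind also narrows the comparison most.

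**Step 3: what is the control?** The Intervention Plan section puts discretionary use of a form (control) next to strict adherence (study). The Implementation section again stresses the study group's adherence to a schedule and has the head nurse check a separate routine care plan. The Harm section expects better treatment adherence in the intervention group but no systematic difference in diabetes management. Together these point to strict versus discretionary pathway nursing, with routine care as shorthand for the latter. The article never says so outright.

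The sentence "Eligible patients receive the TCM nursing pathway for T2DM" names no arm, but it stands under a heading about implementing the pathway, and the next paragraph gives controls routine care. It adds little.

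**Step 4: size, as illustration only.** The article gives no quality-of-life effect or SD, so no bias can be estimated. Inputs: 297 per group (Sample Size Calculation), two-sided P<.05 and an independent-sample *t* test (Statistical Analysis), complete data assumed.

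- Standard error of the difference in SD units: √(2/297) = 0.0821.
- Critical *t* with 592 degrees of freedom: 1.964.
- Smallest significant difference: 1.964 × 0.0821 = 0.161 SD.
- With no true effect and an assumed reporting shift *b*, the noncentrality parameter is *b*/0.0821:

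| Assumed shift (SD) | Probability of P<.05 |
|---|---|
| 0 | 5.0% |
| 0.05 | 9.3% |
| 0.10 | 22.9% |
| 0.15 | 44.6% |
| 0.20 | 68.2% |

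The shifts are assumptions. The table would be the same for any two-arm trial of this size and is no evidence of bias in this one.

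**The case against.** The strongest reply is that the blinding statements do not contradict each other. The blind concerns group assignment, whereas consent and explanation concern the patient's own care. A patient can understand that care without knowing which arm it represents or what the other arm receives. Consent to a proposed care plan reveals no allocation, and both groups' plans are said to be in a pathway form. The article is also a condensation, and what exactly patients are told normally sits in the full protocol and consent form.

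Much of this stands. A reader might infer that patients were in fact unblinded, and the documents do not support that. A reader might also infer that the treating nurses administer the questionnaires. The article says only that researchers collect baseline data with standardized questionnaires and does not say who administers the later ones.

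The reply does not remove the point. Distributing a form named for the intervention and explaining openly visible care are stated procedures, not omitted detail, and they work against the stated blind.

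On the control arm, a reader might infer two irreconcilable descriptions. That goes too far: the Intervention Plan, Implementation and Harm sections largely reconcile as strict versus discretionary nursing. Whether the TCM-specific treatments belong to both arms depends partly on the pathway form in Multimedia Appendix 1, which is not shown. What remains is a label that does not match the contrast the text describes.

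**Conclusion.** The concern holds in a limited form. As described, the design does not give the quality-of-life and satisfaction outcomes the protection that the single-blind label implies. Whether patients learn their arm is not established, and the size of any bias is unknown. This conclusion assumes that the article's account of what patients receive and are told is accurate, and that no unreported step withholds arm-identifying information. If there is such a step, stating it would answer this part.

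Separately, the comparison appears to be strict versus discretionary pathway nursing, and calling the control routine care invites a broader conclusion than that contrast supports. The two parts are independent, and neither strengthens the other. Both should be corrected before results are reported.

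**What to change.** 1. State what arm-identifying information is withheld from patients and how. If none is, replace single-blind with open-label wherever it appears, and interpret quality of life and satisfaction as unblinded patient-reported outcomes.
2. For assessments still to come, have both questionnaires self-completed without nurses who know the assignment. If this is already the practice, say so.
3. Give the analyst coded arm labels until the analysis is locked. This does not repair the patient blind, but it guards the analysis choices at little cost.
4. Define the control arm once, use that definition throughout, and limit the trial question and conclusion to that contrast.

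**Cost.** Rewording, a coded data export and a change in how the remaining questionnaires are completed. The design label becomes less favourable and the conclusion narrower. With 202 of 594 patients randomized at the time of writing, 594 − 202 = 392 planned patients could still be covered in full. Assessments already made in the first 202 cannot be redone, though their later follow-up visits could be covered where still outstanding.

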#### Outcomes

Researchers use standardized questionnaires to collect baseline data. The primary efficacy indicator is a quality of life scale (the Diabetes-Specific Quality of Life Scale) [11]. Secondary efficacy indicators include the length of hospital stay, medical costs, blood glucose control, patient symptom scores, patient satisfaction, and the level of health knowledge acquired at admission. Data are collected 1 day before discharge and at 4 weeks, 12 weeks, and 24 weeks after discharge.

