**Methods:**

This study uses a prospective, randomized, single-blind, parallel-controlled design. Based on sample size calculations, the study will include 594 patients with diabetes, with 2 groups of 297 patients: an observation group will receive a TCM nursing program based on clinical pathways, while a control group will receive routine care. Both groups will be evaluated before and after the intervention using assessment indicators. The primary outcome is the quality of life score, measured by a diabetes-specific quality of life questionnaire. Secondary outcomes include hospital stay duration, medical expenses, health knowledge, blood glucose control, symptom scores, and patient satisfaction.

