The evolution of national standards and their integration with nursing practices have increasingly shifted the focus toward nursing pathways aligned with these standards. This development combines nationally standardized nursing protocols with nursing pathways to create a coherent, interconnected, and progressive nursing model. Pathway-based TCM nursing interventions built on TCM clinical pathways standardize the care of single diseases, promote systematic intervention processes, highlight the efficacy and unique features of TCM, and make nursing operations more standardized. This enables nurses to provide planned and anticipatory care based on structured procedures. A preliminary retrospective analysis of clinical data from 4196 patients with diabetes revealed that integrating traditional Chinese nursing techniques with clinical treatments effectively alleviated patients’ discomfort. Nurses found this approach more practical and valuable in standardizing care, reducing variability, lowering costs, and improving care quality for patients with T2DM [8,9]. Nevertheless, no research has yet examined the simultaneous clinical application of these two nursing methods, which is the aim of our study.

Thus, we conducted a prospective, randomized, single-blind, parallel-controlled trial to further investigate the impact on patient outcomes of integrating nationally standardized nursing protocols with TCM nursing programs based on clinical pathways. These outcomes include hospitalization indicators (eg, length of stay and medical costs), self-management (health knowledge), clinical efficacy (blood glucose control, clinical symptoms, and quality of life), and patient satisfaction. We expect that the findings of this study will provide robust evidence for delivering personalized care, standardizing procedures, improving patients’ quality of life, and enhancing self-care and medication adherence after discharge.

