### Principal Findings

This study focuses on comparing health knowledge and scores in the 2 groups, aiming to optimize an innovative model for the TCM nursing pathway for T2DM. This approach should help enhance the standardization and precision of clinical nursing practices. Its application in the clinic will combine theory with practice, providing high-level clinical evidence through prospective research. The goal is to establish a high-quality TCM nursing pathway that will expand the international influence of TCM and support economic and public health development.

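### The health-knowledge outcome is tied to admission, which contradicts the article's own data-collection schedule, and two later sections present this secondary outcome as the main comparison

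*Protocol article*

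**What the plan says.** In the protocol article, the Outcomes section names the diabetes-specific quality of life scale as the primary efficacy indicator. It ends its list of secondary indicators with "the level of health knowledge acquired at admission". No other indicator in that list carries a time point of its own. The section opens with a separate statement about baseline: "Researchers use standardized questionnaires to collect baseline data". It closes with the schedule: "Data are collected 1 day before discharge and at 4 weeks, 12 weeks, and 24 weeks after discharge".

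The abstract's Methods paragraph has no admission qualifier. It says "Both groups will be evaluated before and after the intervention using assessment indicators", and then "Secondary outcomes include hospital stay duration, medical expenses, health knowledge, blood glucose control, symptom scores, and patient satisfaction". The Introduction also places health knowledge, under self-management, among the outcomes on which the programme's impact is to be studied.

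Two later sections give health knowledge a different rank. Results: "This study primarily aims to compare health knowledge, comprehension, and scores between the 2 groups". Principal Findings: "This study focuses on comparing health knowledge and scores in the 2 groups".

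**The concern.** An efficacy outcome has to be measured after the treatment has had a chance to act. Admission is when patients receive admission education, are assessed for eligibility and are assigned to a group (Intervention Plan; Implementation of the TCM Nursing Pathway for T2DM). A knowledge score fixed at that point is a baseline characteristic. Comparing it between arms would say nothing about the nursing pathway.

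The uncertainty about rank adds to this. If health knowledge is secondary, a loose time point is a limited problem. If it is what the study mainly compares, as two sections say, the time point and the status of the outcome both need to be fixed. As printed, an analyst could choose among admission, discharge and three follow-up visits, and could present the result as either secondary or central, while still pointing to a sentence in the article for support.

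**Working it through.** The article gives no effect size, variance or target difference for health knowledge, so there is no figure of the plan's to reproduce. Its only design calculation, 297 per group, uses satisfaction rates of 74.5% and 85% and does not involve this outcome. The check is therefore a comparison of statements, plus one conditional calculation.

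**1. When is health knowledge measured?**

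| Place | What it implies |
|---|---|
| Outcomes, list of secondary indicators | At admission |
| Outcomes, schedule sentence | One day before discharge, then weeks 4, 12 and 24; no admission visit |
| Outcomes, opening sentence | Baseline questionnaires, mentioned apart from the efficacy indicators |
| Abstract, Methods | Assessment before and after the intervention; no admission qualifier |
| Introduction | A patient outcome of the programme; no admission qualifier |
| Implementation of the TCM Nursing Pathway for T2DM | Relevant data gathered and evaluated at discharge |

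One statement points to admission. The others either point to a later time or treat health knowledge as something the programme should change. The contradiction lies within the Outcomes section itself, between one sentence and the next.

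**2. What would the literal reading do?** Inputs: two-sided testing at P<.05 (Statistical Analysis) and 1:1 randomization (Randomization Method). Let Y0 be the score at admission, before the pathway is delivered.

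- Under valid randomization, E[Y0 | study group] − E[Y0 | control group] = 0.
- The probability of a significant result is then the test's size, 0.05, whatever the true effect on later knowledge. Power would equal alpha.

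This follows from treating the variable as a pure baseline value. It does not apply if the score is compared at discharge or later.

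**3. What rank does the outcome have?**

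| Place | Status |
|---|---|
| Abstract, Methods | Quality of life primary; health knowledge secondary |
| Outcomes | Quality of life primary; health knowledge secondary |
| Results | Health knowledge named first in the primary aim; quality of life not named in that sentence |
| Principal Findings | Health knowledge named as the focus; quality of life not named in that sentence |

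The two sections that define outcomes agree with each other. The two narrative sections do not agree with them.

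**The case against.** The strongest reply is that this is one badly chosen phrase. The schedule follows it immediately, contains four times, and none of them is admission. The abstract, the Introduction and the pathway description all fit measurement after the intervention. The word for knowledge being gained may also refer to education that begins on admission, since health education is one of the three components of the pathway form; the score could then be taken at the listed visits. On that view the remedy is largely in the text already.

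Much of this stands. A reader might infer that the outcome cannot show an effect, that its test has power equal to alpha, or that the trial's headline would rest on a pre-treatment measure. The documents do not support those stronger statements. No passage says that the score is taken before any intervention; that is inferred from what happens on admission. The Statistical Analysis section is general and names neither health knowledge nor a time point. Results and Principal Findings do not mention admission. Nor does the article show that selection at entry would be reported as benefit: how patients are allocated is a separate question from how this outcome is defined.

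Three things remain. First, the schedule sentence does not clearly override the phrase. It is general and cannot time every listed indicator (length of hospital stay, for example, is not re-measured at 24 weeks), whereas the phrase is specific to this outcome. Second, the education reading helps only in part. Admission education is described as given around the eligibility assessment and group assignment, not as a feature of the study arm, so a measure of what it achieved would largely miss the pathway. Third, the mention of scores in Results and Principal Findings might be meant to include quality of life, but neither sentence says so, and health knowledge comes first in both.

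**Conclusion.** The finding holds as an inconsistent outcome definition, not as a demonstrated failure of the design. The admission wording contradicts the schedule in the next sentence and the before-and-after evaluation in the abstract. The rank given to health knowledge in Results and Principal Findings contradicts the abstract and Outcomes.

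On the literal reading the outcome carries no information about the intervention (expected difference zero, 5% chance of significance). On the reading that most of the article supports, measurement from discharge onward, that figure does not apply and the defect is one of wording. The article does not state which is intended, though the balance favours the second. The primary outcome and the sample size are not affected.

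It is worth correcting because it concerns a printed efficacy outcome, leaves both time point and emphasis open, and can still be settled without knowledge of results: the abstract states that no statistical analysis has been done. The 5% figure assumes valid randomization and a score taken before the pathway begins.

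**What to change.** 1. In Outcomes, delete the admission qualifier and define the outcome as the health-knowledge score one day before discharge. If the questionnaire is also given at 4, 12 and 24 weeks, name those results as supportive.
2. Use any admission score only as a baseline covariate in the between-group comparison (for example, analysis of covariance of the discharge score on group and admission score), in place of the unadjusted two-group test in Statistical Analysis. The article indicates that baseline questionnaires are collected but does not say that health knowledge is among them. If it was not collected, the discharge comparison stands without the covariate.
3. Reword the aim in Results and the focus in Principal Findings so that quality of life is primary and health knowledge secondary, as in the abstract and Outcomes.

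Cost: a few sentences and one covariate. No new data are needed if the questionnaire is already given at the scheduled times, and recruitment targets do not change. The correction should be dated before the analysis begins.
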